### Statistical Analysis and Power Analysis

We will present descriptive statistics (eg, proportions, means, SD, and medians) and bivariate correlation measures for variables collected at baseline. To assess the overall effect of the treatment phase (baseline, postintervention, and follow-up) on primary (eg, GD symptom burden, psychological distress, and time spent gaming) and secondary continuous outcome measures, we will conduct repeated measures mixed-effect ANOVA with time as a fixed factor and patient as a random factor; post hoc pairwise comparisons with Bonferroni corrections will be conducted to determine differences in outcome variables across treatment phases. This approach is essentially equivalent to repeated measures ANOVA but will enable us to control individual variability and perform analyses including all cases provided each patient has 1 valid pre- or postoutcome value. In addition, we will conduct logistic mixed-effect model analyses to assess the effect of time on binary outcome measures (ie, symptom improvement).

All tests will be 2-sided with the α level set at .05. Based on previous CBT-based therapy studies for GD that indicate medium-to-large effect sizes from pre- to posttest for symptom burden, time playing, and mental health improvement [32], we estimate that a minimum of 28 participants would be required to achieve 80% power to detect such differences across all outcome measures (Cohen *f*=0.25). To accommodate a potential attrition rate of 30%, we will enroll a minimum of 37 participants for quantitative analyses. Follow-up univariate logistic regressions will be conducted to explore which baseline characteristics are predictive of participant symptom improvement, defined by subcutoff scores for the GDT, IGDS9-SF, and CORE-OM 34 follow-up. Planned analyses will be conducted apropos of missing data patterns and modified accordingly when needed. The results will be reported as means and odds ratios, respectively, with 95% CIs.

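### A patient random intercept alone gives all three pairwise contrasts one pooled standard error, so individual confidence intervals may be miscalibrated, in a direction not known in advance

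*Protocol article*

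**What the plan says.** All of the model wording stands in the protocol article under Statistical Analysis and Power Analysis.

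- **Purpose and time levels:** "To assess the overall effect of the treatment phase (baseline, postintervention, and follow-up"). That is three phases; the separate pretreatment measurement is not among them.
- **Model:** "we will conduct repeated measures mixed-effect ANOVA with time as a fixed factor and patient as a random factor".
- **The authors' own reading of it:** "This approach is essentially equivalent to repeated measures ANOVA".
- **Contrasts:** "post hoc pairwise comparisons with Bonferroni corrections will be conducted to determine differences in outcome variables across treatment phases".
- **Level:** "All tests will be 2-sided with the α level set at .05". Results are to carry 95% confidence intervals.
- **Sample size:** "a minimum of 28 participants would be required to achieve 80% power to detect such differences across all outcome measures", at Cohen f = 0.25.

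The article names no visit-specific covariance, sphericity correction or robust standard error. Its one clause allowing the analysis to be modified concerns missing-data patterns.

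On timing, Study Design and Setting puts follow-up 3 months after therapy ends. Treatment plans about 15 sessions. Principal Findings gives a range of 5 to more than 20.

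**The concern.** A fixed time effect with patient as the only random factor, and no residual structure named, is a random-intercept model. It assumes that scores vary equally at baseline, post and follow-up, and that every pair of visits correlates equally. Equating the model with repeated measures ANOVA points the same way.

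The design gives reason to doubt this. Therapy lies between baseline and post and nowhere else. It is assembled case by case from different modules, may be given to the patient, the parents or both, and differs in length between patients. If patients respond differently, the variance of the change from baseline need not match the variance of the change after treatment has ended.

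At stake are the intervals for change during treatment, for maintenance afterwards, and for baseline to follow-up. All would be built on one average error term. The planned N of 28 appears to rest on the same assumption.

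**Working it through.** **1. The plan's own figure.** For a one-group repeated measures ANOVA with m time points, the noncentrality is λ = f² · N · m · ε / (1 − ρ), with (m − 1)ε and (N − 1)(m − 1)ε degrees of freedom. From the article: f = 0.25, N = 28, m = 3, α = .05. Assumed, because not stated: ρ = 0.5 and ε = 1 (sphericity).

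λ = 0.0625 × 28 × 3 / 0.5 = 10.5 on 2 and 54 degrees of freedom. Power is 81.2%; at N = 27 it is 79.6%. So 28 reproduces, with sphericity assumed. If sphericity fails:

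| ε | Power at N = 28 | N for 80% power |
|---|---|---|
| 1.0 | 81% | 28 |
| 0.9 | 78% | 30 |
| 0.8 | 74% | 32 |
| 0.7 | 70% | 35 |

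**2. What one pooled standard error does.** For visits i and j the true variance of the difference is V = sᵢ² + sⱼ² − 2·r·sᵢ·sⱼ. With complete data, the compound-symmetry model replaces all three V by their mean. The ratio of model standard error to true standard error is √(mean V / V). Since the model uses the mean, unequal V always leave at least one ratio below 1 (interval too narrow) and at least one above 1 (too wide).

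Worked example with equal SDs of 1 and correlations of .3 (baseline–post), .7 (post–follow-up) and .3 (baseline–follow-up): V = 2(1 − .3) = 1.4, 2(1 − .7) = 0.6, and 1.4. The mean is 3.4/3 = 1.133. The ratios are √(1.133/1.4) = 0.90, √(1.133/0.6) = 1.37, and 0.90.

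**3. Range over assumed covariances.** The article gives no SDs and no correlations, so every row below is an assumption. The setting is N = 28, complete data and the pooled error term on 54 degrees of freedom. The last column is the simulated rejection rate of an unadjusted 5% test under the null (one minus interval coverage). Triplets run baseline–post / post–follow-up / baseline–follow-up.

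| Assumed covariance | SE ratio | Nominal 5% becomes |
|---|---|---|
| Equal SDs, all correlations equal | 1.00 / 1.00 / 1.00 | about 5% each |
| Equal SDs, r = .3/.7/.3 | 0.90 / 1.37 / 0.90 | about 8% / 0.9% / 8% |
| Equal SDs, r = .5/.7/.4 | 0.97 / 1.25 / 0.88 | 6.0% / 1.6% / 8.7% |
| Correlation decays (.6 per 13 weeks), 15 then 13 weeks | 1.06 / 1.12 / 0.87 | 3.8% / 2.9% / 9.2% |
| Same decay, 5 then 13 weeks | 1.42 / 0.95 / 0.85 | 0.7% / 6.8% / 10.1% |
| SDs 1/1.3/1.3, all r = .5 | 1.04 / 0.94 / 1.04 | 4.3% / 6.8% / 4.4% |

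The baseline–post ratio runs from 0.90 to 1.42, so its direction is not determined. Baseline to follow-up is too narrow in four of the five rows that depart from compound symmetry. Paired, contrast-specific tests held 4.7% to 5.2% in the response-heterogeneity scenarios in which they were run.

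**4. Familywise error.** With r = .3/.7/.3 and the Bonferroni level of 1.67% (.05/3), the single-contrast rates are about 3.2%, 0.2% and 3.1%. The chance of any false positive when all three phase means are equal is 5.1%. Over the covariances tried it stayed between about 4.5% and 5.3%. With three phases, if exactly two means are equal only one contrast is null, and its rate here is at most 3.2%, still under 5%.

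**The case against.** **The standard error of the contrasts is not stated.** Pairwise comparisons after repeated measures ANOVA can use paired, contrast-specific errors, and sphericity corrections are common. An article may leave such details to a fuller plan that is not shown. This stands in part, and it is why the point is made on the text as written. But the article goes beyond silence: it names the random structure and says what it is equivalent to. Contrasts taken from that model inherit its single error term.

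**A direction might be inferred.** A reader might conclude that the baseline–post interval is too narrow and the post–follow-up interval too wide, because response varies during therapy and is then maintained. That is plausible, but the documents give no SDs or correlations to establish it, and other reasonable covariances remove or reverse it.

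**Unequal spacing might be blamed.** On plan, about 15 sessions, if weekly, is close to 3 months (roughly 15 against 13 weeks), although baseline precedes therapy by an unstated time. What the article does show is an interval that varies between patients, and an unstructured covariance by visit does not model that.

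**Failed error control might be inferred.** Single-contrast rates do depart from nominal, but step 4 shows that Bonferroni familywise control is essentially intact.

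**It is an exploratory single-arm study.** This is fair, and it limits the weight of the point. It does not justify reporting intervals that a one-line change would calibrate better.

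**Conclusion.** The point holds in a limited form. As written, the model imposes compound symmetry and gives the three contrasts one pooled standard error. If contrast variances differ, which the design makes likely but the documents do not quantify, some individual 95% intervals will be too narrow and others too wide. Which ones cannot be said in advance.

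In the covariances tried with 28 patients, a nominal 5% single-contrast test ran from about 0.7% to 10%. If compound symmetry is true there is no error, and small departures matter little. The harm is miscalibrated individual intervals and lost power wherever the pooled error is too large. It is not a breakdown of familywise error.

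The sample size shares the assumption: 81% power at ε = 1 and about 74% at ε = 0.8, both with an assumed correlation of 0.5. This is a cheap improvement to the analysis, not a flaw that undermines the study.

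**What to change.** Keep the time model, but replace the patient random intercept with an unstructured 3×3 residual covariance over baseline, post and follow-up. Fit it by REML with Kenward-Roger degrees of freedom, and take the Bonferroni pairwise contrasts and their intervals from that fit. Fall back to a simpler heterogeneous structure only if the model does not converge, and name that structure in advance. Patients with incomplete data still contribute, so the plan's own reason for preferring a mixed model is kept.

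Add one sentence saying that N = 28 assumes sphericity and a between-visit correlation (0.5 reproduces the figure), with the power that remains if sphericity fails.

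The cost is a line or two of wording and no new data. Statistically, six covariance parameters are estimated instead of two, and the contrasts have somewhat fewer degrees of freedom (27 instead of 54 with 28 complete cases).

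### The 80% power at 28 participants is attached to pre- to posttest differences, but the Bonferroni-corrected pairwise test that would show them has less than that at the planned effect size

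*Protocol article*

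**What the plan says.** All of this stands in the Protocol article, Methods, Statistical Analysis and Power Analysis.

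- **Lead analysis:** a "repeated measures mixed-effect ANOVA with time as a fixed factor and patient as a random factor", over three phases (baseline, postintervention, follow-up).
- **Differences between phases:** "post hoc pairwise comparisons with Bonferroni corrections will be conducted to determine differences in outcome variables across treatment phases".
- **Test level:** "All tests will be 2-sided with the α level set at .05".
- **Basis of the effect size:** earlier studies of CBT-based therapy that showed "medium-to-large effect sizes from pre- to posttest for symptom burden, time playing, and mental health improvement".
- **Power:** "a minimum of 28 participants would be required to achieve 80% power to detect such differences across all outcome measures", with Cohen f=0.25.
- **Enrolment:** at least 37, to allow for 30% attrition.

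The section gives no within-patient correlation. It does not say which test the figure of 28 was computed for.

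**The concern.** The phrase about such differences most naturally points back to the pre- to posttest effects named just before it, so the article reads as claiming 80% power for the change from before to after treatment. An omnibus F test over three phases does not show that change. It shows only that the three means are not all equal. The article gives the task of saying which phases differ to pairwise tests at a level three times stricter than the one quoted with the power.

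If 28 was derived for the omnibus test, the comparison that most readers will look for first has less power than stated. A significant overall effect of time without a significant baseline-to-posttreatment comparison would then be an ordinary result, and nothing in the section prepares the reader for it.

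**Working it through.** **Inputs from the article:** f=0.25; two-sided α=0.05; n=28; three phases, hence three pairs and 0.05/3=0.0167 per pair.

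**Assumptions not in the article:** within-patient correlation ρ=0.5 (varied below), sphericity, complete data.

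**1. Reproducing the 28.** For a one-group repeated-measures F test over m visits, the noncentrality is λ = n·m·f²/(1−ρ), with df (m−1) and (n−1)(m−1). With m=3 and ρ=0.5, λ = 28×3×0.0625/0.5 = 10.5 on 2 and 54 df, and power is 81.2%. At n=27 it is 79.6%, so 28 is the minimum, as stated. This derivation is not unique:

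| Visits | ρ | Minimum n | Power |
|---|---|---|---|
| 3 | 0.5 | 28 | 81.2% |
| 2 | 0.6 | 28 | 81.4% |
| 4 | 0.4 | 28 | 80.8% |
| 2 | 0.5 | 34 | 80.8% (72.3% at n=28) |

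**2. From f to the pre-post difference.** Cohen f is the SD of the three means (divisor 3) in units of the outcome SD, so the pre-post difference d depends on the pattern of means:
- Gain fully held at follow-up (means 1, 0, 0): SD = √2/3, so d = 0.25×3/√2 = 0.530.
- Linear change to follow-up (1, ½, 0): SD = 1/√6, so the full range is 0.25×√6 = 0.612, and pre-post is half of it, 0.306.
- Follow-up midway back to baseline (1, 0, ½): pre-post is the full range, 0.612. This is the largest d that f=0.25 allows with three means.

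**3. Power of the pairwise test at n=28.** The standardised paired effect is dz = d/√(2(1−ρ)), which equals d at ρ=0.5. The noncentrality is dz·√28. The first figure in each cell uses 27 df (paired t) and the second 54 df (pooled error).

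| Pattern | d | dz·√28 | Power at 0.0167 | Power at 0.05 |
|---|---|---|---|---|
| Gain held | 0.530 | 2.81 | 60.4% / 63.2% | 77.2% / 78.7% |
| Linear | 0.306 | 1.62 | 19.5% / 20.7% | 34.6% / 35.6% |
| Most favourable | 0.612 | 3.24 | 74.9% / 77.6% | 87.8% / 88.9% |

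The Bonferroni test reaches 80% at about d=0.65 (80.5%, 27 df), above anything f=0.25 implies here.

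**4. Other correlations, gain held, 27 df.** Power is 44.1% at ρ=0.3, 71.8% at 0.6 and 84.9% at 0.7. But at ρ=0.6 and 0.7 the three-visit omnibus test would need only 23 and 17 participants, so those values do not explain 28. If 28 came from two visits at ρ=0.6 (d=0.50), the Bonferroni pre-post power is 65.8%.

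**5. Is Bonferroni needed with three phases?** If all three means are equal, the omnibus test guards the error at 5%. If exactly two are equal, only one true null pair is left, and it is tested at 5%. So pairwise tests at 0.05 made only after a significant omnibus test control the familywise error (closed testing). A simulation (n=28, ρ=0.5, normal data, pooled error, 40,000 runs) gives familywise error under equal means of 0.051 for this sequence and 0.044 for Bonferroni. With the gain held, pre-post power is 74% for the sequence and 63% for Bonferroni.

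**The case against.** **Powering the omnibus test is ordinary practice.** The mixed-effect ANOVA is the lead analysis, the pairwise tests are called post hoc, and f is the ANOVA effect metric. No section names baseline to posttreatment as the primary contrast. This stands as far as it goes: an 80% labelled as omnibus power would be unobjectionable. But the 80% is attached to differences whose antecedent is pre- to posttest, and the pairwise tests are what determine differences.

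**The true power cannot be known.** A reader might infer that pre-post power simply is about 60%, or that 28 can only have come from the three-visit omnibus test. The article supports neither. The 60% rests on ρ=0.5 and a fully held gain, and 28 arises in at least two other ways. The article also expects medium-to-large effects, and f=0.25 is the medium end. At d=0.80 and ρ=0.5 the Bonferroni test has 94.6% power.

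**The practical harm is limited.** In the same simulation, the omnibus test is significant without the Bonferroni pre-post comparison in 18% of runs if the gain is held and about 60% if change is linear. It is significant with neither baseline comparison (to posttreatment or to follow-up) in only about 3%. Improvement at some point would thus usually still be shown.

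**The numbers are minima.** If 37 provide data, Bonferroni power at d=0.53 is 76-78%. If 30% of 37 are lost, about 26 remain (37×0.70=25.9) and it is 56-59%, although the mixed model can also use partly observed patients.

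**Bonferroni is valid.** It is conservative here but not an error. The study also calls itself exploratory and acknowledges the limits of a single arm.

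**Conclusion.** The point holds as a mismatch between the stated power and the test that delivers the stated comparison. With three phases, n=28, ρ=0.5 and sphericity, the Bonferroni baseline-to-posttreatment test has between about 20% and 78% power across the patterns of means examined. It stays below 80% for every pattern consistent with f=0.25, because 0.612 is the largest pre-post d that f allows. The two-visit route to 28 (ρ=0.6) also leaves it below 80%.

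The direction is firm. The exact size is not, because the correlation and the course to follow-up are assumptions. It should not be inferred that 28 is miscalculated, since it is correct for the omnibus test under conventional inputs, or that the study needs more patients to be worth running.

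**What to change.** 1. Label the 80% as power of the omnibus test of time over three phases, and state the assumed within-patient correlation and sphericity.
2. Report the power of the baseline-to-posttreatment comparison separately, with its range over plausible patterns and correlations.
3. Replace the Bonferroni correction with unadjusted pairwise tests made only after a significant omnibus test. This is justified only while the model has exactly three phases. If the separate pretreatment assessment listed for some measures entered as a fourth, the shortcut would no longer control the familywise error.

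The cost is rewording and a less favourable stated power; no extra patients or visits are needed. The change does not restore 80% for the pre-post comparison: the sequence gives about 74% with the gain held and about 35% with linear change. Naming baseline to posttreatment as the single primary contrast at 0.05 is optional. It gives 77-79% at d=0.53 and would make the follow-up comparisons secondary. Any change of test should be fixed before outcome data are analysed.

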## Methods

### Study Design and Setting

This study has a single group with a pretest, posttest, and 3-month follow-up design, as well as measures at each session. It is conducted in routine care and the participants are treatment-seeking patients. This study will be carried out at a single site, Gamingprojektet Maria Malmö, which is an outpatient clinic for problematic gaming behavior and GD in Skåne, Sweden. The participants will be offered a module-based psychotherapy that is a combination of interventions from CBT and FT. The treatment will be given by psychologists with a 5-year education in clinical psychology and psychotherapy, social workers with 1-year training in psychotherapeutic counseling, and psychotherapists with 2.5 years training in psychotherapeutic counseling. The treatment can be given as an individual treatment with the patient, a family treatment with only the parents, or a family treatment with both the parents and the patient. Most treatments will be conducted with 1 clinician per treatment, but exceptions can be made if there is a high level of conflict between the patient and the parents. Assessment points include baseline, which is the assessment period; the start of therapy (pretreatment period); the end of therapy (posttreatment period); and the follow-up after 3 months. In addition to these quantitative measures, we will also conduct qualitative interviews with patients and relatives about their views on the outcome, acceptability, and eventual negative experiences of the treatment, which will be presented in a separate paper.

A Transparent Reporting of Evaluations With Nonrandomized Designs 2004 flow diagram [44] of this study’s design is shown in Figure 1. This study is registered with ClinicalTrials.gov (NCT06018922). Recruitment started March 17, 2022, and will close on August 30, 2024.

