### Outcome Measures

This study consists of children, adolescents, and adults, as well as their parents. The patients will have different outcome measures depending on whether they are children (aged 13-15 years) or adults (aged 16 years and older). When the patient is a child, some outcome measures will also be collected from parents. An overview of outcome measures and assessment points is shown in Tables 1 and 2.

**Table 1 table1:** Measures’ and measurements’ points for adults, aged 16+ years.

Measure	Outcome	Assessment	Treatment period			
		Baseline	Pretreatment	Weekly	Posttreatment	Month 3
CORE-OM 34^a^	Primary	✓	✓		✓	✓
GDT^b^	Primary	✓			✓	✓
IGDS9-SF^c^	Primary	✓			✓	✓
Time spent gaming	Primary	✓	✓	✓	✓	✓
How do you feel?	—^d^			✓		✓
Demographic	—	✓				
MINI^e^ interview	Secondary	✓			✓	
GAF^f^	Secondary	✓			✓	
NODS-PERC^g^	Secondary	✓			✓	
Social media disorder	Secondary	✓			✓	
Game motives	Secondary	✓			✓	
Emotion regulation	Secondary	✓			✓	
Alcohol use	Secondary	✓			✓	
Substance use	Secondary	✓			✓	
Harm severity of gaming	Secondary	✓			✓	
Working alliance	Acceptability					
Treatment satisfaction	Acceptability					

^a^CORE-OM 34: Clinical Outcomes in Routine Evaluation–Outcome Measure 34 questions.

^b^GDT: Gaming Disorder Test.

^c^IGDS9-SF: Internet Gaming Disorder Scale–Short-Form.

^d^Not applicable.

^e^MINI: Mini International Neuropsychiatric Interview.

^f^GAF: Global Assessment of Functioning.

^g^NODS-PERC: National Opinion Research Centre Diagnostic Screen for Gambling Disorders–Preoccupation, Escape, Risked Relationships, and Chasing.

**Table 2 table2:** Measures’ and measurements’ points for children, aged 13-15 years.

Measure	Outcome	Assessment	Treatment period			
		Baseline	Pretreatment	Weekly	Posttreatment	Month 3
RCADS^a^-child	Primary	✓	✓		✓	✓
RCADS-parent	Primary	✓	✓		✓	✓
GDT^b^	Primary	✓			✓	✓
IGDS9-SF^c^	Primary	✓			✓	✓
GAIT^d^-parent	Primary	✓			✓	✓
Time spent gaming	Primary	✓	✓	✓	✓	✓
How do you feel?	—^e^			✓		
Demographic	—	✓				
MINI^f^-kid interview	Secondary	✓			✓	
CGAS^g^	Secondary	✓			✓	
NODS-PERC^h^	Secondary	✓			✓	
Social media disorder	Secondary	✓			✓	
Game motives	Secondary	✓			✓	
Emotion regulation	Secondary	✓			✓	
Alcohol use	Secondary	✓			✓	
Substance use	Secondary	✓			✓	
Harm severity of gaming	Secondary	✓			✓	
Working alliance	Acceptability				✓	
Treatment satisfaction	Acceptability				✓	

^a^RCADS: Revised Child Anxiety and Depression Scale.

^b^GDT: Gaming Disorder Test.

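### The claim that 28 participants give 80% power for all outcome measures holds only for measures taken by every patient at three visits, not for the age-specific distress scales or the two-visit secondary outcomes

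*Protocol article*

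**What the plan says.** Under Statistical Analysis and Power Analysis the article states that "we estimate that a minimum of 28 participants would be required to achieve 80% power to detect such differences across all outcome measures", with a single effect size of Cohen f=0.25. It adds "All tests will be 2-sided with the α level set at .05". The effect size is drawn from earlier CBT studies of symptom burden, playing time and mental health.

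The model is described in the same section: "we will conduct repeated measures mixed-effect ANOVA with time as a fixed factor and patient as a random factor". Time has three phases: "To assess the overall effect of the treatment phase (baseline, postintervention, and follow-up) on primary". The same model is meant to serve "on primary (eg, GD symptom burden, psychological distress, and time spent gaming) and secondary continuous outcome measures".

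Study Design and Setting confirms one group: "This study has a single group with a pretest, posttest, and 3-month follow-up design". Enrolment is set from the 28: "To accommodate a potential attrition rate of 30%, we will enroll a minimum of 37 participants for quantitative analyses".

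Outcome Measures then divides the instruments by age: "The patients will have different outcome measures depending on whether they are children (aged 13-15 years) or adults (aged 16 years and older". The tables and the Primary Outcome Measures section give this picture:

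- GDT, IGDS9-SF and time spent gaming: primary, both age groups, ticked at baseline, posttreatment and month 3.
- CORE-OM: primary, ages 16 and over only.
- RCADS-child, RCADS-parent and GAIT-parent: primary, ages 13-15 only.
- Every row labelled Secondary: ticked at baseline and posttreatment, not at month 3.

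No pooled or standardised distress score is described.

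**The concern.** A repeated-measures sample size of this kind applies to one outcome, measured in all the counted patients at the counted number of visits. The article extends it to every outcome, but its own tables show that many outcomes break one of those two conditions.

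Psychological distress is one of the three primary constructs, so this is not confined to minor endpoints. A reader who meets an inconclusive CORE-OM or RCADS result would set it against a stated 80% power that those scales do not have at the stated sample size. For the secondary outcomes, the stated phases and the stated visit schedule disagree, so the power basis of the three-phase test does not carry over.

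**Working it through.** **Inputs from the article.** One group; three phases in the model; two-sided alpha 0.05; target power 80%; f=0.25; 28 evaluable patients.

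**Assumptions, not in the article.** Correlation between visits rho=0.5 and sphericity. CORE-OM and RCADS are also ticked at pretreatment, but the stated model uses three phases, so m=3 is used for them.

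**Formula.** For a within-patient time effect with n patients and m visits, the F statistic has df1 = m-1, df2 = (n-1)(m-1) and noncentrality lambda = n × m × f² / (1-rho). Here f² = 0.0625.

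**Step 1: the article's own figure.** n=28, m=3: lambda = 28 × 3 × 0.0625 / 0.5 = 10.5, df 2 and 54, power 81.2%. At n=27 power is 79.6%. So 28 is the minimum and the figure reproduces.

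**Step 2: age-specific distress scales, three visits, 28 evaluable in total.** The splits are illustrations, because the age mix is not given.

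| Patients on the scale | lambda | df | Power |
|---|---|---|---|
| 14 (of 14/14) | 5.25 | 2, 26 | 47.6% |
| 20 (of 20/8) | 7.5 | 2, 38 | 65.1% |
| 8 (of 20/8) | 3.0 | 2, 14 | 26.6% |

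The qualitative result needs no correlation: two scales given to separate age groups cannot each have 28 patients when there are 28 in all. For 28 evaluable in the smaller group, the total would have to be 28/0.5 = 56 at an even split, or 28/0.4 = 70 at 60/40.

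**Step 3: secondary outcomes, two visits, everyone measured.** n=28, m=2: lambda = 28 × 2 × 0.0625 / 0.5 = 7.0, df 1 and 27, power 72.3%. n=33 gives 79.5% and n=34 gives 80.8%, so 34 is the minimum.

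**Step 4: sensitivity to the correlation.** Minimum n for 80% power at f=0.25:

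| rho | Three visits | Two visits |
|---|---|---|
| 0.4 | 33 | 40 |
| 0.5 | 28 | 34 |
| 0.6 | 23 | 28 |

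At rho=0.6 a sample of 28 does serve two visits (81.4%), but the planned three-phase model would then need only 23. In each row the two-visit requirement exceeds the three-visit one.

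**Step 5: sensitivity to holding f fixed.** If f=0.25 over three visits comes from a gain d that is fully kept at follow-up, then f = d × √(2/9), so d = 0.530 SD. The two-visit f is d/2 = 0.265. Power at n=28 becomes 77% and the minimum becomes 30.

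**The case against.** Several points on the other side have force.

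- **The power sentence may concern only the primary constructs.** It speaks of differences in symptom burden, playing time and mental health, and trials are not usually powered for secondary outcomes. This weakens any demand that the secondary outcomes reach 80%. It does not rescue the sentence, because mental health is the age-split construct.
- **A reader might infer that the secondary analysis cannot be run.** The article does not support that. With two visits the time factor has two levels and the mixed model reduces to a paired comparison. What stands is a mismatch between the stated phases and Tables 1 and 2.
- **A reader might infer that every secondary outcome has two visits.** That is true of the rows labelled Secondary. Secondary Outcome Measures also lists therapeutic alliance and treatment satisfaction, which have at most one ticked visit, so no change over time can be tested for them.
- **A reader might take 72% and 34 as the true figures.** They depend on an unstated correlation and on keeping f at 0.25 when the number of visits changes (Steps 4 and 5).
- **Enrolment is a minimum of 37 and may be exceeded.** With no attrition, 37 gives 84.1% for two-visit measures taken by everyone. Yet the 37 is there to absorb 30% loss, and 37 × 0.7 is about 26. Even with no loss, an 18/19 split gives 60% and 62% for distress.
- **The study is single-arm and described as exploratory,** and f=0.25 is the low end of the medium-to-large range it cites. This limits the consequences but does not make the sentence correct.

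**Conclusion.** The statement is wrong as written, because it covers all outcome measures. The figure of 28 is itself sound for GDT, IGDS9-SF and time spent gaming at rho=0.5, and nothing here undermines it for those measures.

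The age-split part is firm: CORE-OM cannot share 28 evaluable patients with RCADS and GAIT-parent and leave each with 28. How far power falls is not known, because the age mix is not given; 48% for each scale at 14/14, and 65% and 27% at 20/8, are illustrations. A reader might conclude that distress is analysed at half the sample size, but that holds only for an even split.

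The secondary-outcome part is a firm mismatch between the stated phases and the tables. Its size, 72% power at 28 and 34 needed, is conditional on f=0.25 and rho=0.5.

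**What to change.** 1. Limit the 80% power statement to GDT, IGDS9-SF and time spent gaming, and state the correlation assumed.
2. State power for CORE-OM and for RCADS by age group at the expected age mix, and do the same for GAIT-parent in the children. A pooled standardised distress score is an optional alternative. It should not be required: it would create a new primary endpoint from scales with different content, and it assumes a common standardised effect across them.
3. Describe the analysis of outcomes labelled Secondary as a baseline-to-posttreatment contrast. If a power figure is given, state the effect size and correlation behind it.
4. Say that alliance and satisfaction are not analysed for change over time.

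The cost is wording and a short recalculation, with no new data collection. The downside is that the stated power for distress becomes less favourable.
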